### The InnoWell Platform Description

The InnoWell Platform is being embedded within traditional face-to-face and Web-based mental health services, and it is being offered to consumers presenting to those services as part of standard clinical care. It is a Web-based platform, and it can be accessed via traditional computing and mobile devices. As outlined in Textbox 2, the platform allows consumers to complete Web-based clinical assessments to understand their needs; explore their personalized dashboard of results, including current symptoms, level of functioning, and health history (see Figure 1); select from recommended care options (eg, fact sheets, apps, etools, and other Web-based systems) to support their mental health and well-being (see Figure 2); track their progress (in real time); share their dashboard and plan with their health professional(s) to support care.

### Participant Procedures

Participants will use the platform of their own accord as part of their standard clinical care with the mental health service. No other participation is required. All survey data are part of the functionality of the platform, which participants complete as part of standard clinical care through their service. The surveys provide assessment across a range of biopsychosocial domains, including psychological distress, suicidal thoughts and/or behaviors, social and occupational functioning, depressed mood, anxiety, sleep-wake cycle, social connectedness, psychosis-like experiences, mania-like experiences, alcohol use, tobacco use, self-harm, physical health, posttraumatic stress, eating behaviors, and body image. These domains, along with the associated surveys configured in the platform, are determined by services, in conjunction with the researchers to meet the needs of their consumers. Table 1 provides an example of the surveys that may be included across a sampling of biopsychosocial domains.

**Figure 1 figure1:**
[figure not shown]
Sample personalized dashboard of results.

**Figure 2 figure2:**
[figure not shown]
Sample clinical and nonclinical care options.

**Table 1 table1:** Example domains and surveys.

Example domain	Survey
Anxiety	Overall Anxiety Severity and Impairment Scale [23] Generalized Anxiety Disorder Scale [24]
Depression	Quick Inventory of Depressive Symptomatology [25] Patient Health Questionnaire [26]
Functioning	Instrumental Activities of Daily Living and Physical Self-Maintenance Scale [27] Activities of Daily Living Index [28]
Trauma	Primary Care Posttraumatic Stress Disorder Screen for Diagnostic and Statistical Manual of Mental Disorders, Fifth Edition [29] Posttraumatic Stress Disorder Checklist [30]
Suicide behaviors	Columbia-Suicide Severity Rating Scale [22]

Completion of the surveys serves to populate a participant’s dashboard, which comprises health cards reflecting the scores (eg, mild, moderate, and high) generated from the participant’s responses (see Figure 1). The abbreviations under the scores reflect the time since the survey was last completed by the participant. For example, “1M” indicates the survey was completed one month earlier, and “14m” indicates the survey was completed 14 min earlier. By clicking on a health card in their dashboard, the participants can learn more about the biopsychosocial domain (eg, *This card tracks your symptoms of depression. Some signs of depression include feelings of worthlessness or losing interest in enjoyable activities*.). Links to psychoeducational resources are also available for further details about symptoms and treatment options. Each health card also contains a range of different care options, commonly known as interventions, to help the participant in managing a particular area of health. Care options are divided into 2 types: clinical and nonclinical (Figure 2). Clinical care options require a health professional’s involvement, such as individual therapy and group therapy. In contrast, a participant can immediately access and begin using nonclinical care options, such as apps, etools, or other systems, without the support of a health professional.

Given the emphasis on suicide prevention, the InnoWell Platform has been built to include immediate access to crisis support options. At any time when engaging with the platform, a participant has access to the “I need help now” button (see Figure 3), which provides contact details for crisis services (eg, Lifeline, Beyond Blue, and Kids Helpline). As described previously, these support options also appear as a pop-up directly after the participant scores low, moderate, or high on the suicidal thoughts and/or behaviors health card. When a participant scores high on this health card, a notification of suicide risk is also triggered for the treating health professional requiring clinical action.

**Figure 3 figure3:**
[figure not shown]
The “I need help now” button.

### Configuration

The InnoWell Platform is highly configurable, allowing each service to adapt the technology to the needs of its consumer base. Although there is a set of core biopsychosocial domains that all services will be encouraged to assess (ie, psychological distress, suicidal thoughts and/or behaviors, psychosis-like experiences, mania-like experiences, social and occupational functioning, self-harm, tobacco use, alcohol use, social connectedness, depression, anxiety, and posttraumatic stress), the measures used to evaluate these areas can be tailored to the service. Similarly, the algorithms used to derive the thresholds for each domain will be based on the most appropriate psychometrics for that population (eg, young people, veterans, and older adults). As the platform is implemented across multiple health services and accumulates more data, these algorithms will become digitally smart.

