### Primary Objective

The primary objective of this clinical trial (Australian New Zealand Clinical Trial Registry ACTRN12618001676202) is to validate the algorithms used to derive stage-based stepped care on data collected by the platform and previously published staging criteria [15]. To do this, 4 independent ratings of stage-based stepped care will be compared: (1) platform generated, (2) health professional, (3) multidisciplinary team via consensus, and (4) expert-clinician reference group (comprising 3 or more academic health professionals with “area of research expertise” in stage-based stepped care for mental ill health). This expert group will review the clinical data of a subset of randomly generated consumers and independently allocate clinical stage.

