### Outcomes

#### Primary Outcome

The platform-generated assignment of stage-based stepped care derived from an algorithm calculated from data collected by the platform will be compared with that allocated by the health professional working directly with the consumer, the within-service multidisciplinary consensus team, as well as by an independent expert-clinician reference group, all of which will rely on previous published clinical staging criteria [15]. For example, to meet criteria for Stage 2 or higher for depression, the disorder needs to have features indicative of more severe disorders, including psychomotor retardation, agitation, impaired cognitive function, severe circadian dysfunction, psychotic features, brief hypomanic periods, severe neurovegetative changes, or severe suicidality. Although a clinician will assess these features as part of standard clinical care to assign clinical stage, the platform will rely on the scores on several health cards (ie, depression, mania-like experiences, psychotic-like experiences, alcohol use, and eating behaviors and body image) for this purpose. The primary outcome will be the reliability of the ratings across these 4 methods of assigning clinical stage as assessed using Cohen kappa coefficient.

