### Ongoing Development of Functionality

Qualitative and quantitative data will be gathered from all users of the platform, including consumers, as well as health professionals and service staff, to inform the iterative redevelopment of the platform, including site-specific customization of any new required functionality, as well as (re)configuration of content, questionnaires, and algorithms. Furthermore, the data collected during iterative user-testing sessions (covered under site-specific ethics approvals from relevant Human Research Ethics Committees) will help to monitor, evaluate, and provide ongoing feedback about the quality, acceptability, and usability of the platform for continuous improvement of the platform.

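### The staging algorithm is planned to change on accumulating data during its own validation, with no locked version named, so a kappa pooled over the trial would describe no single algorithm

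*Protocol article*

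**What the plan says.** The Primary Objective section of the protocol article sets out to "validate the algorithms used to derive stage-based stepped care on data collected by the platform", together with published staging criteria. Four ratings are compared: the platform, the treating health professional, the service's multidisciplinary team, and an expert group that reviews a random subset of consumers. The Primary Outcome section adds: "The primary outcome will be the reliability of the ratings across these 4 methods of assigning clinical stage as assessed using Cohen kappa coefficient".

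The same section explains how the platform arrives at its rating: "the platform will rely on the scores on several health cards (ie, depression, mania-like experiences, psychotic-like experiences, alcohol use, and eating behaviors and body image".

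Two other sections describe planned change. Configuration first says that "the algorithms used to derive the thresholds for each domain will be based on the most appropriate psychometrics for that population", and then: "As the platform is implemented across multiple health services and accumulates more data, these algorithms will become digitally smart". It also lets each service tailor the measures used. Ongoing Development of Functionality says that data from consumers, health professionals and service staff will inform redevelopment of the platform, including "site-specific customization of any new required functionality, as well as (re)configuration of content, questionnaires, and algorithms".

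**The concern.** A validation result is a statement about one defined rule. If thresholds, questionnaires or algorithms change while ratings are collected, the stage stored for a consumer comes from whichever version and configuration applied on that day. One kappa over all consumers is then a mixture. It cannot be attached to the first version, the last version, or the version that services will use afterwards.

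A second issue follows if the consumers who inform an update also enter the kappa. Agreement could then be partly built in. At stake is the trial's main claim, that the algorithm has been validated.

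**Working it through.** The article gives no sample size, target kappa or precision, so there is no stated figure to reproduce. The check is first textual, then illustrative.

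**1. Is change planned?** Yes. Configuration foresees threshold algorithms that develop as data accumulate. Ongoing Development of Functionality lists algorithms and questionnaires among the things to be reconfigured. Neither section gives the mechanism, the timing or the target of the updating.

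**2. Does the change reach the primary outcome?** By inference, yes. The Configuration sentence is about domain thresholds, not the staging rule. But platform stage relies on health-card scores, and Participant Procedures describes those scores as bands such as mild, moderate and high. Moving a threshold can move a band, and so a stage. Ongoing Development of Functionality does not limit its mention of algorithms to thresholds.

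**3. Do configurations differ as well?** Yes. Measures vary by service and thresholds by population. The centers now recruiting already include youth services and a veterans' service. Of the five staging inputs, four (depression, mania-like experiences, psychosis-like experiences, alcohol use) are on the list of core domains, which services are only encouraged to assess. Eating behaviors and body image is not on that list.

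**4. Does anything hold the algorithm still?** Not in the article. Sample Size sets no limit in either direction. Data Collection, Management, and Security allows a data copy at any time, without tying it to a version. No version identifier, freeze, or split between development and validation data is stated. The reference to published criteria constrains the staging rule, but not the thresholds that feed it.

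**5. What could this do to kappa?** Every parameter below is assumed; none comes from the article.

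- Five card scores X1 to X5 are standard normal. The latent severity is L = 1.0·X1 + 0.6·X2 + 0.6·X3 + 0.3·X4 + 0.3·X5 + error, with error SD 1.2. The reference rating is Stage 2 or higher if L > 0.8.
- Variance of L = 1 + 0.36 + 0.36 + 0.09 + 0.09 + 1.44 = 3.34, so SD = 1.83. Prevalence = P(Z > 0.8/1.83) = P(Z > 0.44) = 0.33.
- Kappa = (po − pe)/(1 − pe), where po is the observed agreement and pe = pq + (1 − p)(1 − q) for marginal proportions p and q.
- The untuned first version averages the five cards and cuts at 0.6. Its true kappa is 0.257.
- Tuning means least-squares weights followed by the cut-off that maximises kappa against the reference rating.
- Case A: tune and assess on the same n consumers. Case B: stage each consumer by the version then live, refitted at 25%, 50% and 75% of accrual on earlier consumers only, then pool all consumers.
- There were 400 replicates per n (200 at n = 1,000).

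| n | A: kappa on tuning data | A: true kappa of that version | Difference | B: pooled kappa | B: true kappa of last version | Difference |
|---|---|---|---|---|---|---|
| 50 | 0.672 | 0.445 | +0.227 | 0.311 | 0.422 | −0.111 |
| 100 | 0.611 | 0.485 | +0.125 | 0.392 | 0.477 | −0.085 |
| 200 | 0.583 | 0.505 | +0.078 | 0.429 | 0.495 | −0.066 |
| 500 | 0.559 | 0.520 | +0.040 | 0.458 | 0.516 | −0.058 |
| 1,000 | 0.547 | 0.524 | +0.023 | 0.462 | 0.522 | −0.060 |

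Differences were taken before rounding, so the last digit can be off by 0.001.

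In Case B the pooled value is low because the first quarter of consumers is staged by the weak first version. That sign assumes that updating improves the rule; updates that made it worse could reverse it. The direction therefore depends on facts the article does not give. In both cases the reported kappa differs from that of the version left in use.

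**The case against.** The strongest reply has four parts.

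*The quoted sentence is about thresholds.* Configuration says they follow the psychometrics of each population, not stage ratings, and staging follows published criteria. This stands, and it makes the effect on stage an inference. It does not remove the effect, because stage is computed from card scores and algorithms are named again among the items to be reconfigured.

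*No one says that the same consumers tune and test.* A reader might infer from the shared platform data that the reported agreement will be inflated. The documents do not support that. It would need tuning against the clinician, team or expert ratings, and use of those same consumers in the kappa. The article states neither and excludes neither. The data behind reconfiguration are described broadly, and the accompanying user testing is about quality, acceptability and usability.

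*This is a condensed article.* Version identifiers, data cuts or version-specific analyses may be in a full protocol or analysis plan, and the article never says that kappa will be pooled over versions. This also stands, and it makes the mixture conditional on pooling. The point does not rest on the omission alone, because the article affirmatively plans to change the object it is validating.

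*Re-scoring is not always possible.* Where measures differ by service or questionnaires have changed, a locked version may lack its inputs. This is correct and limits the remedy. It is also a reason to decide early, since each questionnaire change can make earlier responses harder to re-score.

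**Conclusion.** The point holds in conditional form. The article plans for the algorithm to change on accumulating data while it is being validated, and it names no locked version and no separation of updating from validation data. If kappa is pooled over the trial, it will mix versions and configurations and belong to no identifiable algorithm.

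The direction of bias is open. Kappa may be too high if the same consumers' stage ratings tune and test the rule, or too low for the final version if each consumer is staged by the version live at the time. The size for this trial is unknown. The illustrative range of +0.02 to +0.23 in the first case and −0.06 to −0.11 in the second rests on an assumed data model, an assumed refit to stage labels and assumed sample sizes. It shows that the choice can matter, not how much it will matter here.

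**What to change.** In Primary Outcome, state the following:

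- One algorithm version per population (inputs, thresholds and staging rule) is frozen and numbered, and is locked before the expert ratings are unsealed.
- For the primary kappa, stored survey responses are re-scored with that version wherever its required inputs were collected. The number of consumers who cannot be re-scored is reported, by service.
- The primary kappa uses only consumers, or whole services, whose data were not used to build or update the locked version.
- Results for any other version are reported separately and labelled as development.

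The cost is version control and a re-scoring step. Some early consumers will serve for development only, and some will drop out of the primary kappa because they cannot be re-scored. Updates to the live platform may continue.

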### Education and Training Requirements

As stated previously, the implementation of clinical staging models is relatively new to clinical psychiatry [15], and therefore the education and training requirements of health professionals will need to be scoped to ensure consistency of application in each health service. As required, the training will cover the theoretical and scientific underpinnings of the model, the clinical assessment requirements, detailed criteria used to assign stage-based stepped care, the application of the model to subsyndromal, prodromal, or mixed syndromes, and the clinical utility of the model for the purposes of planning, implementing, and monitoring treatment. The method of training delivery may vary from service to service to ensure access and broad distribution.

### Outcomes

#### Primary Outcome

The platform-generated assignment of stage-based stepped care derived from an algorithm calculated from data collected by the platform will be compared with that allocated by the health professional working directly with the consumer, the within-service multidisciplinary consensus team, as well as by an independent expert-clinician reference group, all of which will rely on previous published clinical staging criteria [15]. For example, to meet criteria for Stage 2 or higher for depression, the disorder needs to have features indicative of more severe disorders, including psychomotor retardation, agitation, impaired cognitive function, severe circadian dysfunction, psychotic features, brief hypomanic periods, severe neurovegetative changes, or severe suicidality. Although a clinician will assess these features as part of standard clinical care to assign clinical stage, the platform will rely on the scores on several health cards (ie, depression, mania-like experiences, psychotic-like experiences, alcohol use, and eating behaviors and body image) for this purpose. The primary outcome will be the reliability of the ratings across these 4 methods of assigning clinical stage as assessed using Cohen kappa coefficient.

#### Secondary Outcome

Service-level performance data regarding improvements in safety and clinical quality will be derived from the platform, with an emphasis on identification and rapid response to consumers endorsing suicidal thoughts and/or behaviors (see Figure 4). Outcomes will include the percentage of consumers endorsing suicidal thoughts and/or behaviors across 4 severity levels (ie, none, low, medium, and high) at service entry, the number of suicide escalations (ie, notifications to health professionals) for a specific period and during an entire episode of care, and time between suicide escalation and an action by a health professional (eg, call to consumer, schedule follow-up appointment, and contact emergency services).

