Key features of stage-based stepped care.Provide broad and holistic initial screening, followed by more targeted mental health assessment for those who endorse screening questionsThe intensity of the intervention should be matched to the consumer’s level of need as determined by clinical stageProvide parallel interventions for risk factors associated with poor outcomes (eg, unemployment, alcohol, and/or other substance misuse)Employ proactive monitoring of treatment progress and outcomes

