### The InnoWell Platform

Through a process of participatory design with lived experience, health professionals, and service staff (including administration and management), we have developed a Web-based platform (the InnoWell Platform) that supports the prevention, early intervention, treatment, and continuous monitoring of mental ill health and maintenance of well-being in people aged 2 years and older [20]. The platform is a customizable digital tool kit that operates through existing service providers who utilize the system to provide their consumers with access to evidence-based assessments and feedback, intervention options, and outcome monitoring. It does this by collecting, storing, and reporting personal and health information back to consumers and their health professionals to promote collaborative care partnerships that aim to improve the management of mental ill health and maintenance of well-being. This platform uses multiple sources of information to develop a comprehensive understanding of the consumers’ needs and track their progress over time. This primarily involves Web-based self-reported psychometric measures from both consumers and their health professionals, as well as objective behavioral data collected via third-party integrations. Textbox 2 highlights the functionality built into the InnoWell Platform.

Specifically, in relation to suicide prevention, the InnoWell Platform employs a suicide escalation protocol derived from previous work [18]. In the current platform, suicidal thoughts and/or behaviors are assessed using 2 self-report surveys: Suicidal Ideation Attributes Scale [21] and Columbia-Suicide Severity Rating Scale [22]. Suicidal ideation without plan or intent in the past month triggers a pop-up for the consumer in the platform, providing details for crisis support services. Self-report of suicidal ideation with a plan and/or intent and/or a suicide attempt within the past 3 months triggers both the pop-up for the consumer and sends a notification to the consumer’s health professional, requiring a clinical care action (eg, telephone contact, action safety plan).

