### Secondary Objective

In accordance with the Fifth National Mental Health and Suicide Prevention Plan [9], the secondary objective of this clinical trial is to reduce the rate of suicidal thoughts and/or behaviors by promoting access to comprehensive services and reducing barriers to care, as well as improving service quality and evidence-based clinical interventions. It is hypothesized that use of the platform within traditional mental health services will facilitate earlier identification and rapid service response (eg, earlier appointment with a health professional) to high levels of suicidal thoughts and/or behaviors.

InnoWell Platform functionality.Multidimensional assessment across a range of domains (eg, sleep, anxiety, mood, physical health)Suicidal thoughts and/or behaviors and at-risk mental state identification and subsequent escalation to required interventionDashboard of results across the range of biopsychosocial domainsAlgorithms to determine severity of needs across these biopsychosocial domainsAlgorithms to allocate clinical stage and suggested levels of careReal-time data tracking and interactive progress reportShared care planning between treating health professional and consumerVideo-visit with a health professionalSupport person input and health information sharingCoordination of care across multi-disciplinary servicesAggregate service performance indicator dashboard

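### The escalation count can mix new, repeated and pre-entry suicide attempts, so a change in it cannot by itself be read as a change in safety under care

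*Protocol article*

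**What the plan says.** Under Outcomes, Secondary Outcome, the Protocol article introduces the measures with "Service-level performance data regarding improvements in safety and clinical quality will be derived from the platform" and places the emphasis on identifying suicidality and responding quickly. It names three measures: the distribution of severity at service entry, "the number of suicide escalations (ie, notifications to health professionals) for a specific period and during an entire episode of care", and the time from an escalation to an action by a health professional.

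The trigger is described twice. The InnoWell Platform section has "Self-report of suicidal ideation with a plan and/or intent and/or a suicide attempt within the past 3 months triggers both the pop-up" and goes on to say that the health professional is notified as well. Participant Procedures puts it in terms of the score: "When a participant scores high on this health card, a notification of suicide risk is also triggered for the treating health professional requiring clinical action". Neither description makes an exception for an attempt that has already been notified, or for one that preceded service entry. Neither says whether repeat alerts are kept or suppressed.

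No survey schedule is given: "Participants will use the platform of their own accord as part of their standard clinical care with the mental health service". The Secondary Objective states that "the secondary objective of this clinical trial is to reduce the rate of suicidal thoughts and/or behaviors".

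**The concern.** A look-back trigger and a count of notifications do not fit together well when the count is meant to describe what happens under care. A consumer who attempted suicide shortly before presenting, and has had no plan, intent or attempt since, would truthfully answer yes at each survey until the 3 months have run out. Each yes meets the written trigger, and each resulting notification falls within the service's period total and episode total.

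Two readings of the data would then be unsafe. A service that surveys recent attempters more often would show more escalations than another service with the same events. And attempt-driven counts would fall some weeks after entry because the look-back on pre-entry attempts expires, which could be taken for improvement. This matters because the count is offered as information on improvement in safety. It is also the only one of the three listed measures that follows how often suicidality is flagged after entry: the severity distribution is taken at entry, and the third measure is a response time.

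**Working it through.** The article gives no expected escalation count, so there is no planned figure to reproduce. The check is a count under the written rule.

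**Inputs from the article.** Look-back for an attempt: 3 months, taken as 13 weeks or 91 days (The InnoWell Platform). Unit counted: notifications (Secondary Outcome).

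**Assumptions.** The survey interval is not stated, so a range is shown. The attempt is reported truthfully each time, no other trigger is active, and repeat alerts are not suppressed.

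**1. Attempt before entry.** With the attempt *d* weeks before entry, a survey at entry and then every *i* weeks, notifications = floor((13 − *d*)/*i*) + 1.

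| Attempt before entry | every 4 weeks | every 2 weeks | every week |
|---|---|---|---|
| 1 week | floor(12/4)+1 = 4 | floor(12/2)+1 = 7 | floor(12/1)+1 = 13 |
| 4 weeks | floor(9/4)+1 = 3 | floor(9/2)+1 = 5 | floor(9/1)+1 = 10 |

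New attempts under care: 0 in every cell. The notifications stop 13 − *d* weeks after entry, that is after 12 or 9 weeks, with no new event at any point.

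**2. Attempt under care.** With surveys every *k* days at a random phase, the mean number of notifications per attempt is 91/*k*.

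| Interval *k* (days) | Per attempt | Per 10 attempts |
|---|---|---|
| 7 | 13.0 | 130 |
| 14 | 6.5 | 65 |
| 30 | 3.03 | 30.3 |
| 91 | 1.0 | 10 |
| 182 | 0.5 | 5 |

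Between weekly and 91-day surveys, the same 10 attempts differ 13-fold in the count (130/10).

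**3. Where the effect ends.** With surveys more than 91 days apart an attempt can be notified at most once, so there is no repetition, and some attempts are never notified (0.5 per attempt at 182 days). An attempt within the 91 days before entry is still counted once at an entry survey.

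**4. Would a denominator help?** Only in part. In the 1-week example every survey inside the window is positive: 4/4, 7/7 or 13/13. Dividing by completed surveys removes the frequency effect for that consumer, but the old event is still carried forward.

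**The case against.** The strongest case on the other side is that repetition is inferred. The article states a trigger condition and is silent on repeat alerts, it is a condensed account, and the platform may well suppress them. Survey frequency is also assumed. The textbox on stage-based stepped care has "Employ proactive monitoring of treatment progress and outcomes", but that is a general principle and not a schedule, and with sparse surveys there is no repetition. This stands, and it is why the point is conditional. It does not remove the point, because the article itself fixes the unit as notifications and does not restrict them to new events or to events after entry.

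A reader might go further and infer that the count mainly reflects pre-entry history multiplied by survey frequency, and so says nothing about safety. The documents do not support that. Ideation with plan or intent is a separate trigger that can reflect the consumer's current state, and no split between the triggers is given. Nor does the article say that fewer escalations means safer care. Given its emphasis on identification and rapid response, a notification count is a reasonable measure of detection and workload. Entry severity and response time are reported beside it, and Data Analysis adds reliable change and effect sizes from rating scales.

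It is also tempting to say that time to action should be measured on the first notification of each event only. That does not hold either: every notification requires action, and dropping later ones would hide slow or absent responses to them.

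**Conclusion.** The point holds in a limited form. As written, the outcome can count one attempt several times and can include attempts made before entry, so it depends on survey frequency and on case mix at entry. A change over time, or a difference between services, cannot by itself be read as a change in safety under care.

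The size depends on facts that the article does not give. If alerts are not suppressed, one attempt contributes on average about 13 notifications with weekly surveys, about 3 with 30-day surveys and 1 with 91-day surveys. If alerts are suppressed, or surveys are more than 3 months apart, only the single counting of a pre-entry attempt remains. The share of all escalations that this affects is unknown, because the mix of triggers is unknown. The point concerns only how the outcome is counted and says nothing against the alert rule.

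**What to change.** Leave the alert rule unchanged, state whether repeat alerts are suppressed, and amend the outcome wording as follows:

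- Keep the total number of notifications, labelled as a workload and detection measure.
- Add, as the outcome for safety under care, the number of new escalations: plan or intent reported at that survey, or an attempt not already reported at an earlier survey.
- Report attempts positive at the entry survey once, as entry status.
- Report repeat notifications of an already reported attempt separately.
- Report time to action for all notifications, split into first and repeat notifications of an event.

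The article leaves it unclear whether the 3-month window also governs ideation with plan or intent. If it does, those reports need the same separation of new from already reported.

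The cost is a change of outcome wording and a derivation on data that the platform already collects; no new assessment is needed. The downside arises if attempt dates are not stored. Successive positive answers within 3 months would then have to be linked as one event, and a second attempt inside the window could be missed. For that reason the total notification count should always be shown beside the count of new escalations.
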